## Abstract

**Background:**

Delirium is a frequent complication in older patients admitted to emergency wards, leading to prolonged hospitalization and increased mortality. Although multicomponent interventions are recommended, the evidence for pharmacological prevention remains inconsistent. Protocol-Based Pharmacotherapy Management (PBPM) allows pharmacists to actively manage medications according to a pre-agreed protocol. This study aims to evaluate the efficacy and safety of an “Active PBPM” strategy for delirium prevention compared with that via a standard “Passive PBPM” strategy in elderly emergency patients.

**Methods:**

This single-center, open-label, randomized controlled trial will target patients aged ≥65 years admitted to the general ward of the Department of Primary Care and Emergency Medicine from the emergency room. Eligible patients must have at least one risk factor (e.g., cognitive dysfunction, central nervous system disease). The patients will be randomized (1:1) into either the Active or Passive PBPM group. In the Active PBPM group, pharmacists will intervene to administer prophylactic medication for 3 days, starting on admission day 1. Patients capable of oral intake will receive ramelteon (8 mg) and lemborexant (5 mg) at bedtime. Patients unable to take oral medication will receive a blonanserin patch (20 mg) applied overnight (19:00–06:00). In the Passive PBPM group, pharmacological intervention will be performed only if insomnia occurs. The primary outcome will be the incidence of delirium diagnosed by a psychiatrist based on the Diagnostic and Statistical Manual of Mental Disorders, 5th Edition criteria, within the first 3 days. The secondary outcomes include delirium severity (Delirium Rating Scale-Revised-98), assessed by trained nurses, and safety.

**Discussion:**

This study will determine whether pharmacist-led proactive pharmacological intervention (Active PBPM) reduces the incidence of delirium in high-risk older patients in acute care settings. The findings may establish a new standard of care for the prevention of delirium in emergency medicine.

**Trial registration:**

Japan Registry of Clinical Trials (jRCT) jRCTs051220122. Registered on November 25, 2022

## Protocol version {2}

The current protocol version is 6.0, dated May 26, 2025.

## Background

### Background and rationale {9a}

Delirium is an acute neuropsychiatric syndrome associated with significant adverse outcomes, including prolonged hospitalization, increased mortality, and functional decline [1]. Older patients admitted to emergency departments are at particularly high risk of delirium because of the severity of acute intrinsic and extrinsic diseases, making the prevention of delirium a critical priority in acute care medicine [2].

Current guidelines recommend multicomponent non-pharmacological interventions (e.g., reorientation, early mobilization) as first-line strategies [3, 4]. However, the consistent implementation of these labor-intensive strategies is often challenging in busy clinical settings. Therefore, pharmacological prophylaxis has become an area of interest. In intensive care units (ICUs) and high-care units (HCUs), the alpha-2 agonist dexmedetomidine has garnered attention for delirium prevention [5]. We previously investigated the utility of dexmedetomidine in an HCU setting [6]. However, the use of continuous intravenous sedatives, such as dexmedetomidine, is generally not indicated or feasible in general wards because of the requirement for strict hemodynamic monitoring.

This creates a therapeutic gap for patients in general wards. Unlike ICUs, general wards typically have lower nurse-to-patient ratios, making early detection and management of delirium paradoxically more challenging. Therefore, a safe and effective pharmacological strategy suitable for general ward settings is urgently required. In our clinical practice, we use melatonin receptor agonists (ramelteon), which have some evidence for delirium prevention [7, 8], in combination with dual orexin receptor antagonists (lemborexant), which are known for their favorable safety profile and low risk of inducing delirium [9]. Furthermore, for patients unable to take oral medications, we use a blonanserin patch, a transdermal antipsychotic. Blonanserin is primarily available in Japan and other Asian countries, and its transdermal formulation has been developed specifically in Japan [10]. Although the blonanserin patch is officially indicated for schizophrenia, it is widely used off-label for the treatment of delirium in clinical practice, including at our institution, because of its favorable safety profile and ease of use in patients with swallowing difficulties [11]. However, its efficacy in prevention has not yet been established. This study aims to reposition this agent for prophylactic use.

### Explanation for the choice of comparator {9b}

To consistently implement this multimodal strategy, we focus on the role of pharmacists. In the United States, Collaborative Drug Therapy Management allows pharmacists to actively manage medication therapy [12]. In Japan, a similar system, the Protocol-Based Pharmacotherapy Management (PBPM), has been gaining recognition. We have recently reported the efficacy of PBPM in optimizing antimicrobial therapy [13].

### Objectives {10}

We aim to evaluate the efficacy and safety of a pharmacist-led “Active PBPM” strategy for delirium prevention compared with standard care in elderly emergency patients admitted to general wards.

## Methods: patient and public involvement, and trial design

### Patient and public involvement {11}

No patients or members of the public were involved in the design, conduct, reporting, or dissemination plans of this study. The research protocol was developed by a multidisciplinary team of medical professionals (emergency physicians, psychiatrists, and pharmacists) based on clinical necessity and existing guidelines to ensure patient safety and feasibility in emergency settings.

### Trial design {12}

This single-center, prospective, randomized, open-label, parallel-group, interventional study is designed as a superiority trial. It aims to test the hypothesis that participants in the active PBPM group will have a lower incidence of delirium than those in the passive PBPM group.

A multidisciplinary team will collaborate with clearly defined roles to ensure comprehensive delirium prevention and management:Nurses: Responsible for daily delirium screening using the Delirium Rating Scale-Revised-98 (DRS-R98-J) [14], monitoring sleep–wake cycles, and identifying potential adverse events.Pharmacists: Review medication history and brought-in drugs upon admission to identify high-risk medications, and implement the PBPM for delirium risk reduction.Emergency physicians: Act as attending physicians, supervise overall clinical management, and facilitate the implementation of PBPM interventions in collaboration with pharmacists.Psychiatrists: Provide definitive diagnosis of delirium according to the Diagnostic and Statistical Manual of Mental Disorders, 5th Edition (DSM-5) criteria [15] and provide expert consultation for severe or refractory cases.

## Methods: participants, interventions and outcomes

### Trial setting {13}

This study will be conducted in the general ward of the Department of Primary Care and Emergency Medicine at Kyoto University Hospital (Kyoto, Japan).

### Characteristics of the people who are needed for the trial

**Table Taba:** 

**Characteristic**	**The people we would expect to see included**
Age	≥ 65 years
Sex	No restriction
Gender	No restriction
Race, ethnicity and ancestry	No restriction
Socioeconomic status	No restriction
Geographic location	Kyoto, Japan
Other characteristics relevant to the trial	Present with at least one of the following six delirium risk factors, based on the Japanese national medical reimbursement criteria (“Delirium High-Risk Patient Management Addition”). Importantly, these factors are consistent with the established predisposing factors identified in major epidemiological studies [3, 16] and with international standards (e.g., American Geriatrics Society Beers Criteria) [17]: ・Central nervous system diseases (e.g., cerebrovascular disease, traumatic brain injury) ・Cognitive dysfunction ・History of high alcohol intake (defined as ≥ 4 days/week) ・History of delirium ・Current use of delirium-inducing drugs (e.g., benzodiazepines, corticosteroids, opioids, H2-receptor antagonists, psychotropics, anti-parkinsonian agents, or anticholinergics) ・Post-surgery or scheduled surgery requiring general anesthesia

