## Intervention and comparator

### Intervention and comparator description {15a}

The intervention period will be 3 days. The detailed protocols for the study medications are summarized in Table 1 and Fig. 1.

**Table 1 Tab1:** Protocol for study medications in the Active and Passive PBPM groups

Group	Route	Scheduled medication(19:00)	Action on insomnia
Active PBPM	Oral	**Ramelteon** 8 mg + **lemborexant** 5 mg	Additional **lemborexant** 5 mg (if insomnia persists)
	Non-oral	**Blonanserin** **patch** 20 mg (19:00–06:00)	**Hydroxyzine** (rescue)
Passive PBPM	Oral	None	1. **Ramelteon** 8 mg + **lemborexant** 5 mg 2. Additional **lemborexant** 5 mg (if insomnia persists) (Switch to regular **ramelteon** from next day)
	Non-oral	None	**Hydroxyzine** (rescue)

Intervention period: The protocol-based intervention will be performed for 3 consecutive days from the date of enrollment (day 1 to day 3). Active PBPM group: Pharmacists will actively intervene to initiate prophylactic medications, regardless of the presence of symptoms. Passive PBPM group: Medications will be administered only as symptomatic treatment if insomnia or delirium symptoms are observed. Regular administration in the Passive group: If rescue medication is required for insomnia in the oral intake group, Ramelteon 8 mg will be switched to regular administration at 19:00 from the following day.・Blonanserin patch: In the Active PBPM (non-oral) group, the patch will be applied for 11 h (from 19:00 to 06:00 the following morning)

*Abbreviations*: *PBPM* Protocol-Based Pharmacotherapy Management; *eGFR* estimated glomerular filtration rate

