**Fig. 1 Fig1:**
[figure not shown]
Detailed intervention and assessment schedules by enrollment timing. The timeline varies depending on the timing of enrollment. **A **Standard schedule: Enrollment on day 1 (08:30–17:00), with the 72-h protocol period starting that night. **B **Delayed schedule: Enrollment on day 2 for patients admitted at night or outside regular hours. The gray bar represents the 72-h protocol period. Blue squares indicate medication administration at 19:00 (Active group only). Green triangles indicate twice-daily nurse assessments using the DRS-R98-J at 20:00 and 10:00 (6 assessments total). The red star indicates the final diagnosis of the primary outcome by a blinded psychiatrist using DSM-5 criteria, performed within 3 days after protocol completion

Active PBPM group: Pharmacists will screen for delirium-inducing drugs upon admission. The patients will receive prophylactic medications for three consecutive nights.Oral intake possible: Ramelteon and lemborexant daily at 19:00.Oral intake impossible: The blonanserin patch will be applied daily from 19:00 to 06:00.Passive PBPM group: No prophylactic medications will be administered. Medications will be provided as rescue therapy only if insomnia occurs, following standard care procedures (Table 1).

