### Criteria for discontinuing or modifying allocated intervention/comparator {15b}

Interventions will be discontinued in case of (1) intolerable adverse events, (2) use of prohibited medications, (3) withdrawal of consent, (4) post-enrollment discovery of ineligibility, or (5) significant clinical deterioration or death. No interim analysis is planned for this study. As such, no formal stopping rules for the entire trial have been established based on efficacy or futility. However, the principal investigator may terminate the trial early if unforeseen safety concerns arise.

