### Strategies to improve adherence to intervention/comparator {15c}

Adherence to the study protocol is rigorously maintained through the structured PBPM framework. In this system, pharmacists proactively identify eligible patients and propose medication plans based on the pre-agreed protocol. These plans are then reviewed and formally approved by the attending physicians before any treatment is implemented. This collaborative verification process ensures that the intervention strictly adheres to the trial design. Furthermore, all prescriptions and administrations are recorded in the electronic medical record system, which is regularly reviewed by the research team to monitor and ensure full compliance with the protocol.

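### Anti-parkinsonian treatment is a named route into the trial and no exclusion covers parkinsonism, yet non-oral Active patients are assigned a prophylactic antipsychotic patch with no stated exception

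*Protocol article*

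**What the plan says.** **Entry.** Eligibility criteria {14a} requires one of six delirium risk factors. One is "Current use of delirium-inducing drugs (e.g., benzodiazepines, corticosteroids, opioids, H2-receptor antagonists, psychotropics, anti-parkinsonian agents, or anticholinergics". A patient can therefore qualify on anti-parkinsonian treatment alone.

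**Exclusions.** The same section lists eleven: schizophrenia, antipsychotic use, a stay that cannot exceed 48 h, benzodiazepines from a psychiatrist or psychosomatic physician, CYP3A4 inhibitors, ramelteon or lemborexant, a patch already in place, severe liver dysfunction, severely disturbed consciousness, prior sedatives, and drug abuse. Protocol amendments {31} adds, for day-2 enrolment, prior study drug, hydroxyzine or antipsychotic. Neither place mentions parkinsonism or anti-parkinsonian drugs.

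**Treatment.** On the Active arm, Table 1 says: "Pharmacists will actively intervene to initiate prophylactic medications, regardless of the presence of symptoms". The text with Fig. 1 adds: "Oral intake impossible: The blonanserin patch will be applied daily from 19:00 to 06:00". The dose is 20 mg on three nights. The non-oral Passive row has no scheduled drug, only hydroxyzine for insomnia.

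**The drug.** Background {9a} says that "for patients unable to take oral medications, we use a blonanserin patch, a transdermal antipsychotic". On prophylactic use it says: "However, its efficacy in prevention has not yet been established". Harms {17} includes extrapyramidal symptoms among its pre-specified harms.

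**General safeguards.** Under Trial design {12}, pharmacists "Review medication history and brought-in drugs upon admission to identify high-risk medications, and implement the PBPM for delirium risk reduction". Section {15c} says of the medication plans: "These plans are then reviewed and formally approved by the attending physicians before any treatment is implemented". Section {15b} states: "Interventions will be discontinued in case of (1) intolerable adverse events".

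**The concern.** The criteria name users of anti-parkinsonian drugs as suitable participants, and the treatment table then assigns those who cannot swallow an antipsychotic. The protocol anticipates extrapyramidal symptoms, and these are the patients in whom one would least want to provoke them. The patch is preventive and goes to people who may have no symptoms at all. Randomisation itself creates the exposure, because the same patient in the Passive arm has no scheduled drug.

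What is at stake is an avoidable exposure in a small group. It is not the validity of the treatment comparison.

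**Working it through.** **1. Setting the sections side by side.**

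| Step | Section | Does it stop the exposure? |
|---|---|---|
| Entry on anti-parkinsonian use | {14a} | No; it admits the patient |
| Eleven exclusions | {14a} | No; none applies |
| Day-2 exclusions | {31} | No; they concern drugs already given |
| Active, non-oral: patch for 3 nights | {15a}, Table 1 | No; no exception or alternative |
| Pharmacist medication review | {12} | Not by rule; it looks for drugs that raise delirium risk |
| Physician approval of the plan | {15c} | Only by individual judgement, and after allocation |
| Stopping for adverse events | {15b} | No; it acts after exposure |

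No step gives a rule for these patients.

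**2. The plan's own figures (background only).** The point does not depend on the sample size. At 5% versus 25%, the exact power of Newcombe's interval (upper limit below 0) is 80.3% with 48 per arm and 79.3% with 47. The stated 96 therefore reproduces. The target of 105 gives 105/2 = 52.5 Active patients on average.

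**3. How common must the combination be?** Let q be the share of participants who both take these drugs and cannot take oral medication. With 52 Active patients, at least one exposure is more likely than not when

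1 − (1 − q)^52 > 0.5, that is, q > 1 − 0.5^(1/52) = 0.0132,

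or about 1 in 76 (0.0130 with 53 Active patients). This threshold needs no assumed prevalence.

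**4. Illustrative counts.** The documents give neither the share on these drugs nor the share unable to take oral medication. The shares below are assumptions and are taken as independent.

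| On these drugs | Non-oral | q | Expected Active exposures, 52.5 × q | Extra eligible patients to reach 105, 105/(1 − q) − 105 |
|---|---|---|---|---|
| 3% | 15% | 0.0045 | 0.24 | 0.5 |
| 5% | 30% | 0.0150 | 0.79 | 1.6 |
| 8% | 45% | 0.0360 | 1.89 | 3.9 |

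At the low end, the chance that no Active patient is exposed is 0.9955^52 = 0.79. The last column is the recruitment cost of the exclusion.

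**The case against.** **The document states no contraindication.** This is correct. The protocol nowhere says that the patch is unsafe in parkinsonism. Harms {17} lists extrapyramidal symptoms for the whole trial without tying them to one drug, and Background {9a} describes the patch's safety as favourable. A reader might infer that the protocol knowingly prescribes a contraindicated drug, or that harm at some rate will follow. The documents support neither. They support only this: a drug that the protocol classes as an antipsychotic, in a trial that anticipates extrapyramidal harm, can be assigned to patients admitted on anti-parkinsonian treatment.

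**The article may be condensed.** Figs. 1, 2 and 4 are not shown, and Table 1 defines eGFR without using it, so prescribing cautions may have been trimmed. That possibility remains. But the eligibility list is presented as operative and already screens drug safety in detail (CYP3A4 inhibitors with examples, liver function, existing antipsychotics). Section {5} also calls this document the primary protocol.

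**Clinicians will notice.** They probably will in many cases, because drug history is reviewed on admission and a physician approves each plan. This lowers the likely number exposed. It does not supply a rule, and {15c} describes approval as a means of keeping treatment to the design, which prescribes the patch.

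**There is no contradiction.** This is fair. The inclusion item follows a national reimbursement list of delirium risks. The fault is a gap in the exclusions, not two statements that clash.

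**A stronger reading through the analysis set.** A reader might infer that a refused patch biases the primary analysis, because the full analysis set in {27b} requires a dose. That definition affects any undosed participant, including Passive patients who never need medication. It is a separate and larger matter. At about 0 to 2 patients it adds nothing here, and the safety argument does not rely on it.

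**Conclusion.** The point holds as a safety gap in the stated criteria. The plan as written allows a prophylactic antipsychotic in patients who entered because of anti-parkinsonian treatment, and only individual judgement after allocation stands in the way. The number affected is unknown and probably small: about 0 to 2 Active patients (0.24 to 1.89) under assumed shares that have no source in the documents. The added risk per exposed patient is not given and none is claimed. The sample size and the primary analysis are essentially unaffected. The change should be made because the exposure is avoidable and the remedy is cheap. The conclusion assumes that the full protocol and the figures not shown contain no rule for these patients.

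**What to change.** 1. Add to the exclusions in {14a}: *parkinsonism, or taking anti-parkinsonian agents, in a patient unable to take oral medication*. Check it when eligibility is confirmed, before the allocation seal is opened ({22}, {23}), and identically in both arms. Patients on these drugs who can swallow stay eligible, since their scheduled treatment contains no antipsychotic.
2. Oral intake can be lost after enrolment, so add to Table 1: *the blonanserin patch is not applied to an enrolled patient with parkinsonism or on anti-parkinsonian agents who later loses oral intake; the patient follows the non-oral hydroxyzine row and stays in the analysis as randomised*.

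**Cost.** One exclusion line and one table note. The target of 105 stands. Under the assumed shares, about 0.5 to 3.9 more otherwise eligible patients must be found. The results would not cover non-oral patients with parkinsonism or on these drugs.

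**Limits.** The change does not touch haloperidol, which {15d} allows as rescue for agitation in both arms. That treats a symptom and is not assigned by randomisation, but the investigators should check that the algorithm in Fig. 2 (not shown) deals with these patients. Recruitment was expected to end on 28 February 2026, so the change protects only patients still to be enrolled.

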### Eligibility criteria for participants {14a}

Patients will be eligible if they meet all the following inclusion criteria:Admitted to the general ward of the Department of Primary Care and Emergency Medicine via the emergency departmentAge ≥ 65 yearsPresent with at least one of the following six delirium risk factors, based on the Japanese national medical reimbursement criteria (“Delirium High-Risk Patient Management Addition”). Importantly, these factors are consistent with the established predisposing factors identified in major epidemiological studies [3, 16] and with international standards (e.g., American Geriatrics Society Beers Criteria) [17]:Central nervous system diseases (e.g., cerebrovascular disease, traumatic brain injury)Cognitive dysfunctionHistory of high alcohol intake (defined as ≥4 days/week)History of deliriumCurrent use of delirium-inducing drugs (e.g., benzodiazepines, corticosteroids, opioids, H2-receptor antagonists, psychotropics, anti-parkinsonian agents, or anticholinergics)Post-surgery or scheduled surgery requiring general anesthesia

Patients will be excluded if they meet any of the following criteria:SchizophreniaTaking antipsychoticsUnable to be hospitalized for >48 hTaking benzodiazepines prescribed by a psychiatrist or psychosomatic physicianTaking CYP3A4 inhibitors (e.g., itraconazole, clarithromycin, erythromycin, fluconazole, verapamil, human immunodeficiency virus protease inhibitors)Taking ramelteon or lemborexantBlonanserin patch is already appliedSevere liver dysfunctionSevere disturbance of consciousnessSedatives are used before the start of the studyDrug abuse

### Eligibility criteria for sites and those delivering interventions {14b}

This study will be conducted at a single tertiary care academic hospital (Kyoto University Hospital). The interventions are delivered by licensed medical professionals (physicians, pharmacists, and nurses) affiliated with the Department of Primary Care and Emergency Medicine. All participating pharmacists are trained in the specific PBPM protocol, and psychiatrists provide expert diagnostic confirmation.

